### Subjects

#### Inclusion criteria

Those who are willing to participate in the trial and meet the following conditions will be included: ages 8 to 9 years old; SE (after cycloplegia), − 0.5 D to + 0.5 D; uncorrected visual acuity ≥ 0.8; corneal curvature, 40 D–46 D; with good compliance; and the subject and his/her guardians signed the informed consent form.

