#### Primary outcome measures

The primary outcome measures include MI and SE.

The measurement of SE will be carried out with Nidek ARK-1 refractometer produced by Nidek, Japan. Before measurement, the subjects were given one drop of 0.5% proparacaine hydrochloride eye drops (Alcaine), one drop of 1% cyclopentolate hydrochloride eye drops (CYCLOGYL) 1 min later, and one drop of 1% cyclopentolate hydrochloride eye drops (CYCLOGYL) 5 min later, to induce cycloplegia, getting ready for automatic optometry 30 min later. The measurement will be performed three times successively. Make sure that the maximum-minimum difference in the spherical and cylindrical diopters should be no more than 0.25 D, respectively, and the average value of the three measurement results will be recorded. The SE is defined as spherical diopter plus 1/2 cylindrical diopter. According to existing reports and clinical routines [35], we define myopia as SE ≤ − 0.50 D.

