### Data collection and management

The collection of all baseline data and general information of each subject will be completed within 1 week before the start of the intervention. The general data include gender, age, school grade, number of myopic parents, past history, and medication history. The baseline data include spherical equivalent, axial length, uncorrected visual acuity, corneal curvature, and choroidal and retinal thickness. At 3, 6, 9, and 12 months after recruitment, the SE, axial length, uncorrected visual acuity, and choroidal and retinal thickness will be measured again to observe the changes. The data collection timeline is shown in Figure S4.

The information of each subject will be recorded in the CRF and the electronic database ResMan, with codes and abbreviations used instead of their names to protect privacy. The data in CRF form and ResMan will be independently input and checked by two third-party data administrators unrelated to the test to ensure the accuracy. If the subject requests to withdraw from the trial, the eye condition of the subject will be evaluated as quickly as possible. For suspicious data, the data manager will conduct data recheck query (DRQ) and give feedback to the researcher. The researcher should reply as soon as possible for the doubtful data, and the data manager will modify, confirm, and input the data according to the researcher’s reply. All paper and electronic documents will be kept, and the data printed on thermal paper will be photographed. Therefore, if readers or reviewers have any questions, they can certainly contact the authors for the original data.

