### Statistical analysis

SPSS version 25.0 will be used for data processing in this trial. Only ocular parameters of the right eye will be included for statistical analysis. Analyses will be performed based on a modified intention-to-treat principle and involve only subjects who have both a baseline outcome measurement and at least one post-randomization observation. Last-observation-carried-forward approach will be used to replace missing data.

The measurement data will be expressed as means ± standard deviation or median (interquartile interval), and the counting data will be described by the number of cases (percentage). Fisher’s exact test or Pearson’s chi-square test will be used for trial group comparisons of 1-year cumulative MI. Generalized estimating equations (GEE), with one within-subject factor (time), one between-subject factor (intervention), and their interactions, will be used to compare changes in spherical equivalent, axial length, uncorrected visual acuity, and choroidal and retinal thickness. The covariates in the GEE models include the corresponding baseline measures, age, gender, number of myopic parents, outdoor light exposure time, and near-work time. All the tests of effects will be conducted at a two-sided alpha level of 0.05.

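### The primary comparison of myopia incidence ignores baseline SE, which is measured in every child; the planned test is valid, but adjusting for baseline SE would add power at no cost in data

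*Protocol article*

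**What the plan says.** Under Primary outcome measures the protocol article states that "The primary outcome measures include MI and SE", and that "we define myopia as SE ≤ − 0.50 D". The Sample size section rests on MI alone: 8.41% against 17.65% per year, 80% power, 204 per group, 480 recruited.

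Under Inclusion criteria the entry range is "SE (after cycloplegia), − 0.5 D to + 0.5 D". Under Data collection and management, "The baseline data include spherical equivalent, axial length, uncorrected visual acuity, corneal curvature", and Table 1 schedules cycloplegic SE at enrolment for all subjects.

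Under Statistical analysis, the MI sentence reads "Fisher’s exact test or Pearson’s chi-square test will be used for trial group comparisons of 1-year cumulative MI". It names no covariate and no rule for choosing between the two tests. SE and the other continuous outcomes go into GEE models, for which "The covariates in the GEE models include the corresponding baseline measures, age, gender, number of myopic parents, outdoor light exposure time, and near-work time". The analysis set is limited to children with a baseline measurement and at least one later observation.

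**The concern.** The event is defined on the same variable that is measured at entry. A child may start anywhere from 0 to 1.0 D away from the myopia threshold, so baseline SE is each child's distance from the event. The plan uses this information for the SE analysis and leaves it out of the comparison that determined the trial's size.

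The protocol does not itself call baseline SE a strong predictor of MI. That follows from the threshold definition, and its strength depends on how variable the one-year change in SE is. At stake is the power for the incidence question. Neither bias nor the false-positive rate is in question.

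**Working it through.** **1. The plan's own figure.** Inputs from the Sample size section: π_r = 0.0841, π_c = 0.1765, α = 0.05, power 0.80. With a two-sided z in the printed formula:

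n = (1.960 + 0.842)² × [0.0841 × 0.9159 + 0.1765 × 0.8235] / (0.1765 − 0.0841)²
= 7.849 × (0.0770 + 0.1453) / 0.008538 ≈ 204.4 per group.

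408 / 0.85 = 480. The stated size is reproduced. The formula prints Z at 1 − α, which would give about 161, but 204 agrees with the two-sided test in Statistical analysis, so this is a notation slip.

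**2. Power of the planned tests at 204 per arm.** Exact enumeration at 8.41% and 17.65%, two-sided 0.05: Pearson 80.0%, Fisher 76.0%. Expected events per arm under no difference: 204 × (0.0841 + 0.1765)/2 = 26.6, about 27.

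**3. How informative baseline SE could be.** Assume that 12-month SE = baseline SE + shift + normal noise. Take baseline SE as uniform on −0.5 to +0.5 D and set the control shift so that MI is 17.65%. The one-year control risk is then:

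| SD of change | at −0.4 D | at 0 D | at +0.4 D |
|---|---|---|---|
| 0.3 D | 50% | 9% | 0.4% |
| 0.5 D | 39% | 14% | 3% |

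**4. Power with adjustment.** Same model, 204 per arm, shifts set to give 17.65% and 8.41%, 1,500 runs per setting. The unadjusted Pearson test is compared with a likelihood-ratio test for arm in a logistic model that contains baseline SE. The baseline shape and the SD of change are assumptions, because the protocol gives neither.

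| Baseline SE | SD of change | Pearson | Adjusted | Gain (points) |
|---|---|---|---|---|
| Uniform −0.5 to +0.5 | 0.25 | 79.5% | 89.8% | 10.3 |
| | 0.4 | 79.0% | 85.5% | 6.5 |
| | 0.6 | 78.9% | 83.0% | 4.1 |
| | 1.0 | 79.3% | 80.7% | 1.4 |
| Skewed towards plus | 0.25 | 78.7% | 89.6% | 10.9 |
| | 0.4 | 82.1% | 85.2% | 3.1 |
| | 0.6 | 80.1% | 82.3% | 2.2 |
| | 1.0 | 80.2% | 81.3% | 1.1 |
| Uniform 0 to +0.5 | 0.25 | 80.9% | 85.1% | 4.2 |
| | 0.4 | 80.9% | 83.3% | 2.4 |
| | 0.6 | 77.9% | 79.5% | 1.6 |
| | 1.0 | 78.5% | 79.3% | 0.8 |

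Monte Carlo error on each power is about 1 point. A separate set of runs with uniform baseline gave 80.3% to 88.1% at SD 0.3 D and 81.1% to 85.5% at SD 0.5 D. Type I error of the adjusted test averaged 5.5% over 12 × 500 null runs.

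For scale, the adjusted 85.5% at SD 0.4 D (uniform baseline) is about what the unadjusted test reaches with 240 per arm (85.5% by the normal approximation, 86.3% by enumeration).

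**The case against.** The strongest reply is that nothing here is inconsistent. The trial was sized with an unadjusted two-proportion formula and is analysed with the matching test, which is valid under randomisation and reaches the planned 80%. That stands, and it limits the point to efficiency.

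Three stronger readings are tempting, and the documents do not support them.

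- A reader might infer that chance imbalance in baseline SE makes the MI comparison unreliable. Its type I error already allows for such imbalance; simulated values for Pearson were 3.8% to 4.7%. Adjustment removes noise, not bias.
- A reader might infer that the promised power is not delivered because Fisher's test reaches only 76.0% at 204 per arm. Wording of this kind commonly means Fisher only where expected counts are small, which about 27 per arm are not, and the selection rule may sit in a SAP that is not shown. Moreover, the analysis set keeps any child with one later visit and carries the last value forward, so the analysed number probably lies between 204 and 240 per arm. Exact Fisher power is 79.8% at 222 and 83.0% at 240. The shortfall needs both the choice of Fisher and most of the allowed dropouts having no follow-up at all.
- A reader might infer that every useful covariate is in hand, including hospital. Data collection and management does not list hospital, and only baseline SE was tested in the simulations.

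It is also fair to object that the size of the gain rests on assumed inputs. At the larger SDs, calibrating to the stated incidences forces implausible drift: with a uniform baseline and SD 0.5 D, control children move +0.04 D and treated children +0.30 D on average. In the scenarios where control children drift towards myopia, the gain is about 2 to 11 points. Finally, baseline SE is used in the co-primary SE analysis, but that does not help the MI comparison.

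**Conclusion.** The point holds as a matter of efficiency. The unadjusted comparison is valid and Pearson's test has the planned power, but the plan leaves unused a covariate that defines the distance to the event and is available for every analysed child. Over the range of assumptions examined, the gain from adjustment is about 1 to 11 points of power at 204 per arm. It is about 5 to 8 points for a uniform baseline with SD 0.3 to 0.5 D, and close to nil when the SD is near 1.0 D. These figures assume the incidences in the Sample size section and normally distributed one-year change; the baseline SE distribution and the SD are not in the protocol. The direction of the benefit is secure, its size is not.

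**What to change.** In Statistical analysis, replace the MI sentence with a prespecified logistic regression of 1-year cumulative MI on arm and baseline SE, optionally with age and number of myopic parents. Restrict the model to covariates known at randomisation. The GEE covariate list should not be copied across as it stands, because Table 1 records outdoor light exposure and near work only after allocation.

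Report the arm effect as a standardised risk difference with 95% CI, so that the result stays on the scale used for the sample size. Keep Pearson's chi-square as the unadjusted supporting test and remove the open choice of Fisher's test.

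The cost is analysis wording only. Baseline SE, age and number of myopic parents are already collected, the analysis set already requires a baseline measurement, and no visit, examination or change in sample size is needed.

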## Method/design

### Design of the trial

This parallel, randomized, blank controlled prospective clinical trial will be carried out in the Eye and ENT Hospital of Fudan University and Shuguang Hospital Affiliated to Shanghai University of Traditional Chinese Medicine, two top-rank hospitals in China. The subjects will be randomized in a 1:1 ratio to an intervention group versus a control group. The intervention group will receive auricular acupressure for 12 months, while the control group will not receive any interventions. A series of optical examinations will be performed at baseline, and 3, 6, 9, and 12 months after recruitment. The whole flow of the trial is illustrated in Figure S1 and the schedule is shown in Table 1. During the study, the subjects will be asked to keep a journal to record their compliance. The research staff will inform each subject of the details of the study before intervention, and all the subjects and their guardians will provide written consent before the treatment starts and they will all be given sufficient time to reach the final decision.

**Table 1 Tab1:** Schedule of treatment assessments and data collection

	Enrollment and baseline	Study period					
		Allocation	Post-allocation				Close-out
Time point (month)	-	0	3	6	9	12	
Informed consent	×						
Inclusion/exclusion	×						
General information	×						
Random allocation		×					
Intervention (auricular acupressure)		×	×	×	×	×	
SE (after cycloplegia)	×		×	×	×	×	
Axial length	×		×	×	×	×	
Uncorrected visual acuity	×		×	×	×	×	
Corneal curvature	×						
Retina thickness	×		×	×	×	×	
Choroid thickness	×		×	×	×	×	
Outdoor light exposure			×	×	×	×	
Near work			×	×	×	×	
Concomitant medication	×		×	×	×	×	
Adverse events and other unintended effects			×	×	×	×	
Compliance			×	×	×	×	
Completion summary							×

This trial will follow the Declaration of Helsinki (version 2013) and has been approved by the Ethics Committee of Shuguang Hospital Affiliated to Shanghai University of Traditional Chinese Medicine (approval No. 2020-801-08-01) and registered at www.chictr.org.cn (ChiCTR2000038456).

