#### Recruitment

We will recruit most of the subjects by placing posters in schools, hospitals, and communities, while the rest will be recruited at the outpatient. All the recruitment advertisements will only be published after the trial was approved by the ethics review committee. The respondents will contact the research staff by telephone, WeChat, or in outpatient visit. The researchers will screen the subjects according to the inclusion and exclusion criteria, and collect a part of the baseline data during the screening. The recruitment process will continue until the number of recruits reaches the expected standard. The recruitment process is shown in Figure S1.

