#### Sample size

So far, there is no high-quality randomized controlled trial (RCT) studying the sole use of auricular acupoints in reducing the MI. Increasing outdoor time is the main method well recognized in the prevention of myopia. Therefore, the preventive effect of outdoor activities is used to estimate the efficacy of auricular acupoints. The MI in the intervention group 8.41%/year, and that in the control group is 17.65%/year [32]. When we set α = 0.05, test efficiency 1 – β = 0.80, and the ratio between the two groups 1:1, the calculated required sample size is 204 for each group according to the following equation, that is 408 in total. Then, when the dropout is set at 15% or less, a total of 480 participants should be recruited in this study.
$$ n=\frac{{\left({\mathrm{Z}}_{1-\alpha }+{\mathrm{Z}}_{1-\beta}\right)}^2}{{\left({\pi}_r-{\pi}_c\right)}^2}\left[{\pi}_r\left(1-{\pi}_r\right)+{\pi}_c\left(1-{\pi}_c\right)\right] $$$$ {\pi}_r= MI\ \mathrm{in}\ \mathrm{the}\ \mathrm{intervention}\ \mathrm{group} $$$$ {\pi}_c= MI\ \mathrm{in}\ \mathrm{the}\ \mathrm{control}\ \mathrm{group} $$

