### Randomization and grouping

SPSS version 25.0 will be used to generate random numbers and random distribution table. According to the random sequence, the paper marked with intervention group or control group will be put into a sealed opaque envelope. The subjects will be randomized into an intervention group or a control group at 1:1. The randomization process will be completed by a third party unrelated to the study. Only after the informed consent of the subjects has been obtained and the subjects have completed the baseline data collection, the allocation personnel can inform the acupuncturists of the allocation assignment.

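### The trial runs in two hospitals, but the listed GEE covariates leave hospital out, at a small cost in precision

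*Protocol article*

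**What the plan says.** Under Design of the trial, the protocol article states that the study "will be carried out in the Eye and ENT Hospital of Fudan University and Shuguang Hospital Affiliated to Shanghai University of Traditional Chinese Medicine". It does not say how many children each hospital contributes, or whether enrolment, eye examination and acupressure all take place at both.

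Under Randomization and grouping, "SPSS version 25.0 will be used to generate random numbers and random distribution table", and "The subjects will be randomized into an intervention group or a control group at 1:1". Sealed opaque envelopes carry the sequence. The section mentions neither strata nor blocks.

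Under Statistical analysis, SE, axial length, uncorrected visual acuity, and choroidal and retinal thickness are compared by GEE with time, intervention and their interaction. The adjustment set is spelled out: "The covariates in the GEE models include the corresponding baseline measures, age, gender, number of myopic parents, outdoor light exposure time, and near-work time". Hospital does not appear. Myopia incidence (MI) is handled separately: "Fisher’s exact test or Pearson’s chi-square test will be used for trial group comparisons of 1-year cumulative MI".

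**The concern.** Hospital is settled before randomisation and is known for every child, so it costs nothing to use. One site is an eye and ENT hospital and the other a hospital of traditional Chinese medicine. If both enrol, the children they draw may progress at different rates. A difference of that kind that the listed covariates do not explain adds to the residual variance of the treatment comparison. A chance imbalance in hospital between the arms also goes uncorrected.

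What is at stake is precision for SE, one of the two primary outcomes, and for the secondary outcomes. The planned number leaves little slack: 480 recruited less 15% is 408, which is exactly the number required for MI.

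**Working it through.** **1. The plan's own figure.** The Sample size section gives MI of 8.41% and 17.65% per year, α = 0.05, power 0.80 and 204 per group. With the two-sided normal quantile:

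- variance sum: 0.0841 × 0.9159 + 0.1765 × 0.8235 = 0.2224
- squared difference: 0.0924² = 0.008538
- n = (1.960 + 0.842)² × 0.2224 / 0.008538 = 204.4 per group, against 204 stated
- 408 / 0.85 = 480

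The figure reproduces. I use 204 analysed per arm below. The article gives no power statement for SE, so 80% serves only as a reference level for the GEE outcomes.

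**2. Assumptions.** The article gives neither of these:

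- q, the share of children at one hospital: 0.5, with 0.7 and 0.9 as alternatives.
- d, the hospital difference in the outcome after the listed covariates, in within-hospital SDs: 0.2, 0.3 and 0.5.

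The calculation treats the comparison as one normally distributed outcome at one time point, which is a simplification of the GEE.

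**3. Loss of power.** Leaving out a two-level factor multiplies the residual variance by f = 1 + q(1 − q)d². If the adjusted comparison has 80% power, the unadjusted one has Φ[(1.960 + 0.842)/√f − 1.960].

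| d | f (q = 0.5) | Power, q = 0.5 | Power, q = 0.7 | Power, q = 0.9 |
|---|---|---|---|---|
| 0.2 | 1.0100 | 79.6% | 79.7% | 79.9% |
| 0.3 | 1.0225 | 79.1% | 79.3% | 79.7% |
| 0.5 | 1.0625 | 77.6% | 78.0% | 79.1% |

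The loss is greatest with equal hospitals: 0.4 to 2.4 percentage points.

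**4. Chance imbalance, if the list is not stratified.** With equal hospitals, the hospital share differs between arms by up to 1.96 × √(2 × 0.25/204) = 0.097, or 9.7 percentage points (95% limit). At d = 0.3 this shifts the treatment difference by 0.097 × 0.3 = 0.029 SD. The standard error of that difference is √(2/204) = 0.099 SD. This shift is part of the variance already counted in step 3, so it is not a second cost.

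**5. Validity.** A simulation with 408 children, equal hospitals, individual unstratified allocation and no hospital term (20,000 runs for each d) gave a type I error of 4.9% to 5.3% for d from 0 to 1. There is no sign of inflation.

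**6. If the list was in fact stratified by hospital.** The arms are then balanced on hospital, but a model without it still counts hospital variation as error. The standard error is too large by √f: a factor of 1.005 at d = 0.2 and 1.031 at d = 0.5. The actual two-sided level is 2[1 − Φ(1.960√f)], which is 4.9% and 4.3%. The tests are slightly conservative.

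**The case against.** The best case for leaving the plan alone is that nothing in it is contradictory or invalid. With individual randomisation, a hospital term is an option rather than a requirement. The article condenses a fuller protocol, and its verb for the covariates could be read as not exhaustive. The children are also alike at entry (aged 8 to 9, SE between −0.5 D and +0.5 D), so a large hospital difference in change may be unlikely. Most of this stands, and it is why the point is minor. It does not remove the point: six covariates are named, and a reader would take them as the model.

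Four stronger readings are tempting, and the documents do not support them.

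- *The random list ignores hospital.* A reader might infer this from the Randomization and grouping section, but that section is only silent on strata. Stratification detail is something a condensed article commonly leaves out.
- *Both hospitals enrol, examine and treat.* The article says only that the trial is carried out in the two hospitals. They might divide the roles. Recruitment is described without reference to site: "We will recruit most of the subjects by placing posters in schools, hospitals, and communities, while the rest will be recruited at the outpatient".
- *OCT thickness and axial length are especially exposed, because they depend on instrument and operator.* The GEE compares changes and adjusts for the baseline value. A stable offset between instruments or operators is in that baseline too and is largely absorbed. Only a difference in change is left.
- *The treatment estimate is biased or the test is invalid.* Steps 4 to 6 show ordinary sampling variation, a type I error near 5% without stratification, and a level slightly below 5% with it.

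**Conclusion.** The point holds as a minor improvement to a stated model. The trial is carried out in two hospitals and the listed GEE covariates omit hospital, so between-hospital differences in change in SE and the secondary outcomes stay in the error term. The cost is at most a few points of power: from 80% to about 79.6% at a hospital difference of 0.2 SD and 77.6% at 0.5 SD with equal hospitals, and less with an unequal split. Those differences and the split are assumptions. If only one hospital enrols children, the point falls away. The sample size does not need to change.

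**What to change.** Add hospital as a fixed factor to every GEE model, for SE and for each secondary outcome, provided both hospitals enrol children. Record this in the analysis plan before unblinding. State at the same time which hospitals enrol and whether allocation was stratified by hospital. The term is worth having in either case: it recovers precision if allocation was not stratified, and brings the test back to its nominal level if it was.

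The cost is one model term and a sentence or two of text. This change does not touch the MI comparison, which is a separate unadjusted test.

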### Blinding

Due to the unique feature of the intervention, we can only blind the examiners, data processors, and statisticians but not the interveners or subjects. Before each examination, subjects in the intervention group will be asked to take off the auricular adhesives, which will be checked by the personnel in charge of randomization. During the whole study, the subjects and other researchers are not allowed to disclose the grouping to examiners, data processors, and statisticians. Only when serious adverse events occur and the researchers believe that it is necessary to know the intervention to take effective measures, can the blinding rule be broken. The researchers will be trained strictly before the trial begins.

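### The GEE for spherical equivalent, a primary outcome, adjusts for outdoor and near-work time recorded only after open-label allocation, so its treatment contrast is biased if allocation shifts either behaviour.

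*Protocol article*

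**What the plan says.** All references are to the protocol article; no separate analysis plan is at hand.

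- **Primary outcomes** (Primary outcome measures): "The primary outcome measures include MI and SE".
- **Model** (Statistical analysis): GEE with time, intervention and their interaction "will be used to compare changes in spherical equivalent, axial length, uncorrected visual acuity, and choroidal and retinal thickness".
- **Covariates** (same section): the baseline value of the outcome, age and gender, together with "number of myopic parents, outdoor light exposure time, and near-work time".
- **Timing** (Design of the trial, Table 1): the row "Outdoor light exposure" and the near-work row are marked at months 3, 6, 9 and 12. Neither is marked under enrolment and baseline.
- **Pre-intervention data** (Data collection and management): "The general data include gender, age, school grade, number of myopic parents, past history, and medication history"; and "The baseline data include spherical equivalent, axial length, uncorrected visual acuity, corneal curvature, and choroidal and retinal thickness". Neither list contains outdoor or near-work time.
- **Blinding** (Blinding): "we can only blind the examiners, data processors, and statisticians but not the interveners or subjects".
- **Incidence** (Statistical analysis): one-year cumulative myopia incidence (MI) is compared by Fisher's exact or Pearson's chi-square test, with no covariates.

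**The concern.** Adjusting for a variable fixed before randomisation can gain precision without biasing a linear treatment contrast. Adjusting for a variable measured afterwards is different when allocation can alter it, for two reasons.

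1. Any part of the treatment effect that passes through the behaviour is removed from the estimate.
2. Children with the same recorded outdoor time in the two arms are no longer comparable on whatever else determines outdoor time. If family habits drive both behaviour and refraction, a non-randomised path opens between arm and outcome.

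A shift by arm is plausible here. Families know the allocation. The Intervention section asks guardians in one arm only for three pressing sessions a day (one in the hour after school), a nightly diary and weekly adhesive changes. The Sample size section calls outdoor time the main recognised means of preventing myopia, so the protocol itself treats the covariate as a cause of the outcome. At stake is the SE contrast, together with the axial length, acuity and thickness contrasts that use the same covariate set.

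**Working it through.** **1. Is the timing a table-reading fault?** No. In Table 1 other rows, such as axial length and concomitant medication, keep their baseline mark. The outdoor and near-work rows show the same post-allocation pattern as adverse events and compliance, and the Data collection section agrees. The protocol therefore schedules no pre-randomisation value that the model could use.

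**2. Number per arm.** The point does not rest on the sample size, but its 204 per arm is used below, so it was checked. With MI of 8.41% and 17.65%, two-sided α = 0.05 and 80% power:

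- (1.960 + 0.842)² = 7.849
- 0.0841 × 0.9159 + 0.1765 × 0.8235 = 0.2224
- (0.1765 − 0.0841)² = 0.008538
- n = 7.849 × 0.2224 / 0.008538 = 204.4 per arm; 408 / 0.85 = 480 in total

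The stated figures reproduce.

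**3. Confounding through family habits (assumed inputs; the protocol gives none).** Let the true treatment effect be 0. Outdoor time is scaled to SD 1 within arm and shifted by s between arms. A habit factor has correlation r with outdoor time and is worth g dioptres per SD. Residual SD is 0.45 D. A linear model stands in for the GEE.

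- Within-arm slope of SE on outdoor time: r × g
- Bias of the adjusted contrast: −s × r × g
- Adjusted residual SD: √(0.45² + g²(1 − r²))
- Standard error: residual SD × √(2/204) × √(1 + s²/4). The last factor reflects the correlation of arm with outdoor time.
- Rejection rate: P(|Z + bias/standard error| > 1.96)

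For s = 0.3, r = 0.5, g = 0.2: slope 0.10 D per SD; bias −0.030 D; residual SD √(0.2025 + 0.0300) = 0.482 D; standard error 0.482 × 0.0990 × 1.011 = 0.0483 D; ratio −0.62; rejection 9.5%.

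| s | r | g | Bias (D) | Type I error |
|---|---|---|---|---|
| 0 | 0.5 | 0.2 | 0.000 | 5.0% |
| 0.1 | 0.5 | 0.2 | −0.010 | 5.5% |
| 0.2 | 0.5 | 0.2 | −0.020 | 7.0% |
| 0.3 | 0.5 | 0.2 | −0.030 | 9.5% |
| 0.3 | 0.5 | 0.1 | −0.015 | 6.2% |
| 0.3 | 0.3 | 0.1 | −0.009 | 5.4% |

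Simulation (10,000 replicates per row) agrees to within about 0.001 D and half a percentage point. The unadjusted contrast is unbiased throughout.

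**4. Effect removed.** If a 0.3 SD shift in outdoor time, worth 0.10 D per SD, were the only route of action, the total effect would be 0.3 × 0.10 = 0.03 D. The adjusted estimate would be 0.00 D. Simulation gave 0.031 D unadjusted and 0.001 D adjusted.

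**5. Direction.** A second assumed set-up has a direct effect of 0.10 D and outdoor time worth 0.1 to 0.2 D per hour a day, with or without an unmeasured common cause.

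| Shift (h/day) | True total effect (D) | Adjusted estimate (D) |
|---|---|---|
| 0 | 0.10 | 0.10 |
| +0.25 to +0.5 | 0.125 to 0.20 | 0.06 to 0.10 |
| −0.5 | 0.00 to 0.05 | 0.10 to 0.14 |

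The adjustment can hide benefit or create it. A half-hour shift here is about 0.7 SD, since the within-arm SD is 0.70 to 0.76 h. That is well beyond the range in step 3, so this table shows direction and not likely size.

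**The case against.** The case on the other side has four parts.

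- **No shift is shown.** The intervention is a set number of presses in fixed windows and carries no instruction on outdoor time or near work. Without a shift, adjusted and unadjusted estimates agree. This stands. A reader might infer that the SE contrast has simply lost the protection of randomisation; the protocol does not support that unconditional statement.
- **The inputs are assumed.** A reader might take a near-doubling of type I error as the expected result. It needs the largest shift, correlation and habit effect in the range together; milder inputs leave the rate between 5% and 7%. The habit calculation also gives outdoor time no effect of its own, which fits poorly with the protocol's view of it as preventive. This stands, which is why a range starting at no bias is given.
- **The investigators may want the effect of acupressure net of behaviour.** This is a fair question in an open-label trial without sham. It does not rescue the plan: no such target is stated, the declared principle is modified intention-to-treat, and adjustment would still leave unmeasured confounding between behaviour and refraction.
- **Examiners are blinded and the measures objective.** True, but the problem lies in conditioning on the covariate, not in how the outcome is measured.

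Nor can the choice be left to an analysis plan not shown: the covariate set is already fixed in the article.

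**Conclusion.** The point holds in conditional form. The SE model, and the models for the secondary ocular outcomes, condition on two behaviours recorded only after open-label allocation. The harm depends on whether allocation moves either behaviour, which the protocol neither shows nor quantifies.

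Over the assumed range in step 3, the bias is 0 to about 0.03 D in size and type I error about 5% to 10%. The sign depends on the direction of the shift. These figures take each mechanism alone; if effect removal and confounding acted in the same direction, their biases would add.

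A reader might also infer that both primary outcomes are compromised. They are not: the MI comparison uses no covariates and alone drives the sample size. The point still deserves correction before analysis, because it concerns a primary contrast, the size of the bias cannot be known in advance, and the remedy costs almost nothing.

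**What to change.** Choose one of two changes to the primary SE model, and apply it to the secondary GEE models as well:

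1. Remove outdoor and near-work time. Keep the baseline measure, age, gender and number of myopic parents.
2. Collect outdoor and near-work time at enrolment, before randomisation, by the same measure used later, and adjust for that baseline value only. This is open only where children have not yet been randomised.

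In either case, report the month 3 to 12 values by arm, so that readers can see whether behaviour shifted. Keep the model with post-randomisation behaviour as a labelled sensitivity analysis, stating that it addresses a different question and assumes no unmeasured common cause of behaviour and refraction.

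Cost: a change of analysis wording. The first option may lose a little precision; the second adds one item to the baseline visit.
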